### ***Age and Sex***

Men and women of and over 18 years old.

Women of childbearing potential (WOCBP) must use appropriate method(s) of contraception. WOCBP should use an adequate method to avoid pregnancy for 23 weeks (30 days plus the time required for ipilimumab to undergo five half-lives) after the last dose of investigational drug

WOCBP include any female who has experienced menarche and who has not undergone successful surgical sterilization (hysterectomy, bilateral tubal ligation, or bilateral oophorectomy) or is not postmenopausal. Post menopause is defined as:

- 1) Amenorrhea  $\geq 12$  consecutive months without another cause or
- 2) For women with irregular menstrual periods and on hormone replacement therapy (HRT), a documented serum follicle stimulating hormone (FSH) level  $> 35$  mIU/mL.

Women who are using oral contraceptives, other hormonal contraceptives (vaginal products, skin patches, or implanted or injectable products), or mechanical products such as an intrauterine device or barrier methods (diaphragm, condoms, spermicides) to prevent pregnancy, or are practicing abstinence or where their partner is sterile (eg, vasectomy) should be considered to be of childbearing potential.

WOCBP must have a negative serum or urine pregnancy test (minimum sensitivity 25 IU/L or equivalent units of HCG) within 24 hours prior to the start of investigational product.

Men who are sexually active with WOCBP must use any contraceptive method with a failure rate of less than 1% per year. Men receiving ipilimumab and who are sexually active with WOCBP will be instructed to adhere to contraception for a period of 23 weeks after the last dose of investigational product. Women who are not of childbearing potential (i.e., who are postmenopausal or surgically sterile as well as azoospermic men do not require contraception).

#### ***4.2.2 Exclusion Criteria***

Subjects meeting any of the following exclusion criteria will be excluded from the study:

- 1) Subjects with any contraindications for ipilimumab
- 2) Subjects with active brain metastases or leptomeningeal metastases
- 3) Subjects with metastatic uveal melanoma
- 4) Subjects with active, known or suspected autoimmune disease
- 5) Subjects with a condition requiring systemic treatment with either corticosteroids ( $>10$  mg daily prednisone equivalents) or other immunosuppressive medications within 14 days of treatment
- 6) Subjects with symptomatic effusions on account of pleural, pericardial metastases of melanoma

- 7) Prior treatment with an anti-Programmed Death receptor-1 (PD-1), anti-Programmed Death-1 ligand-1 (PD-L1), anti-PD-L2, or anti-CTLA-4 antibody
- 8) Subjects who had major surgery or radiation therapy within 21 days of starting treatment
- 9) Subjects who are unable to return for follow-up visits as required by this study.
- 10) Subjects with a history of second malignant tumor, other than the common skin cancers – basal and squamous carcinomas, within the past 3 years and uncertainty about the histological nature of the metastatic lesions.

### ***Other Exclusion Criteria***

- a) Prisoners or subjects who are involuntarily incarcerated;
- b) Subjects who are compulsorily detained for treatment of either a psychiatric or physical (e.g., infectious disease) illness.

Eligibility criteria for this study have been carefully considered to ensure the safety of the study subjects and to ensure that the results of the study can be used. It is imperative that subjects fully meet all eligibility criteria.

### ***4.2.3 Discontinuation of Subjects from Treatment***

Subjects will be treated with combination therapy until the completion of 4 cycles of therapy, irPD, subject refusal or excessive toxicity.

Subjects MUST discontinue investigational product (and non investigational product at the discretion of the investigator) (investigational or non investigational treatment) for any of the following reasons:

- Withdrawal of informed consent (subject's decision to withdraw for any reason),
- DLT,
- Any clinical adverse event (AE), laboratory abnormality or intercurrent illness that, in the opinion of the investigator, indicates that continued participation in the study is not in the best interest of the subject,

NOTE: In case of excessive toxicity, if the observed AE leading to treatment discontinuation is unequivocally attributable to only 1 of the 2 investigational drugs, patient might still receive the other drug at the investigator discretion

- Pregnancy (see Section 7.7),

- Termination of the study by NIBIT,
- Loss of ability to freely provide consent through imprisonment or involuntarily incarceration for treatment of either a psychiatric or physical (eg, infectious disease) illness.

All subjects who discontinue should comply with protocol specified follow-up procedures as outlined in Section 6. The only exception to this requirement is when a subject withdraws consent for ALL study procedures or loses the ability to consent freely (i.e, is imprisoned or involuntarily incarcerated for the treatment of either a psychiatric or physical illness).

If a subject was withdrawn before completing the study, the reason for withdrawal must be entered on the appropriate case report form (CRF) page.

## **5 TREATMENTS**

### **5.1 Study Treatment**

All protocol-specified investigational and non-investigational products are considered study drug.

#### ***5.1.1 Investigational Product***

An investigational product, also known as investigational medicinal product in some regions, is defined as follows:

A pharmaceutical form of an active substance or placebo being tested or used as a reference in a clinical study, including products already with a marketing authorization but used or assembled (formulated or packaged) in a way different from the authorized form, or used for an unauthorized indication, or when used to gain further information about the authorized form.

In this protocol, investigational products are SGI-110 and ipilimumab. Astex will supply SGI-110 to Fondazione NIBIT/CRO for this trial. Ipilimumab will be utilized in the study according to the approved dose and schedule of administration for metastatic melanoma.

### 5.1.2 Identification

**Table 5.1.3: Investigational Drug Information**

| Unit                     | Route       | Appearance                                                                |
|---------------------------------|--------------------|----------------------------------------------------------------------------------|
| Ipilimumab
5 mg/mL   | IV infusion | Clear, colorless solution in
50 mg (10 mL) or 200 mg (40
mL) vial |
|                                 |                    |                                                                                  |
| SGI-110 100 mg           | SC          | Dry powder lyophilized                                                    |
| SGI-110 diluent
3 ml |                    | Non- aqueous diluent                                                      |

### 5.1.3 Packaging and Labeling

Study drug will be provided as follows:

Ipilimumab and SGI-110 labels will contain the protocol prefix, batch number, contents, route of administration, storage conditions and appropriate IND caution statement.

### 5.1.4 Handling and Dispensing

Study drug supplied to the sponsor or sourced by the investigator should be stored in a secure area according to local regulations. It is the responsibility of the investigator to ensure that study drug is only dispensed to study subjects. The study drug must be dispensed only from official study sites by authorized personnel according to local regulations.

The investigator should ensure that the study drug is stored in accordance with the environmental conditions (temperature, light, and humidity) as determined by the sponsor and defined in the Investigator Brochure for SGI-110 and ipilimumab. If concerns regarding the quality or appearance of the study drug arise, do not dispense the study drug and contact the sponsor immediately.

Please refer to Section 9.2.2 for information on study drug record retention and 9.3 for destruction instructions

### **SGI-110**

SGI-110 should be reconstituted under aseptic conditions and kept under refrigerated conditions.

Drug product is available as a two-vial system, referred to as (1) SGI-110 for Injection, 100 mg and (2) SGI-110 Diluent for Reconstitution, 3 mL:

- SGI-110 for Injection, 100 mg contains SGI-110, 100 mg of free acid equivalent, as a dry powder lyophile.
- SGI-110 Diluent for Reconstitution, 3 mL contains 3 mL of a non-aqueous diluent for reconstitution.

SGI-110 for Injection, 100 mg vial is stored at 2°C to 8°C in the original packaging until use. SGI-110 Diluent for Reconstitution, 3 mL can be stored at 2°C to 30°C in an upright position until use. Both vials are preservative free and for single use only.

The diluent is comprised of 3 commonly used excipients, propylene glycol, glycerin, and ethanol, that are generally recognized as safe (GRAS). All 3 excipients are pharmaceutically acceptable solvents previously used in drug products approved for SC administration. SGI-110 solution is reconstituted at a maximum concentration of 100 mg/mL for SC administration. Both product and diluent are contained in clear glass vials stoppered with a latex-free rubber stopper and capped with an aluminum flip-off seal. The reconstituted SGI-110 solution is chemically stable for 8 days under refrigerated conditions; however, there are no preservatives in the custom diluent or lyophilized vials. For study centers using the PhaSeal® system for reconstitution of SGI-110, it is recommended to use the Assembly Fixture provided by the manufacturer to attach the PhaSeal® Protector to the SGI-110 lyophilized vial and custom diluent vial, and to filter the final reconstituted product with a 0.2 micron filter. This is to eliminate the presence of foreign material resulting from stopper coring in the final dispensed product.

### ***Ipilimumab***

Ipilimumab (BMS-734016) Injection (5 mg/ml), must be stored refrigerated (2 - 8°C) with protection from light. Ipilimumab injection must not be frozen.

Ipilimumab injection may be stored undiluted (5 mg/mL) or following dilution on 0.9% Sodium Chloride Injection (USP), or 5% Dextrose Injection in PVC, non-PVC/ non-DEHP, or glass containers for up to 24 hours at (2°C - 8°C) or room temperature/room light. This would include any time in transit and the total time for infusion.

## **5.2 Method of Assigning Subjects to a Treatment**

After informed consent has been obtained, the patient will be enrolled into the study by a dedicated software, that will be available to the participant Center, and obtain a patient number. The exact procedures for using the dedicated software will be detailed in a separate document.

Following completion of all Screening Phase evaluation, and checking inclusion criteria site personnel will register the patient to obtain a treatment assignment (STEP2). The e-Clinical system assigns subjects to the SGI-110 dose level.

### ***5.2.1 Dosage and Administration***

#### ***SGI-110 schedule***

SGI-110 will be administered:

Start at 30 mg/m^2 day s.c. on W0, 3, 6, 9 Day 1 - 5 q21 days. Dose Level -1: 15 mg/m^2 day; dose level +1: 45 mg/m^2 day, Dose Level +2: 60 mg/m^2 day for a total of 4 cycles.

SGI-110 is administered by SC injection preferably in the abdominal area; however the thigh and arms may be used. A Luer-Lok disposable syringe should be used when dispensing and administering SGI-110. Due to the slightly viscous nature of the preparation, use of thin-walled subcutaneous needle is highly recommended for ease of subcutaneous administration and subject comfort. SGI-110 should be injected slowly (up to one minute) as some injection site discomfort or pain may be experienced.

If injection site pain is reported upon injection, apply ice packs to the injection site both before and after injection. If the injection site events are reported at subsequent injections despite slow injection and the use of ice packs, pre-treatment with topical or systemic analgesics can be considered. The total amount (in mg) of SGI-110 to be administered will be determined based on the body surface area (BSA). In calculating the BSA, actual heights and weights taken at enrolment should be used. There will be no adjustments to “ideal” body weight or dose modifications related to changes in body weight < +/- 10%. The institutional standard for calculating BSA is acceptable.

The site(s) of SGI-110 SC injections will be captured on the dosing CRF.

#### ***Ipilimumab schedule***

Ipilimumab will be administered:

3 mg/Kg i.v. over 90 minutes on W1, 4, 7 and 10 for a total of 4 cycles.

Ipilimumab is to be administered as a 90-minute IV infusion, using a volumetric pump with a 0.2/0.22 micron in-line filter at the protocol-specified dose. The drug can be diluted with 0.9% normal saline for delivery but the total drug concentration of the solution cannot be below 0.35 mg/ml. It is not to be administered as an IV push or bolus injection. At the end of the infusion, flush the line with a sufficient quantity of normal saline.

### **5.2.2 Dose Escalation**

Dose escalation will be dependent on the available toxicity information (including adverse events that are not DLTs), PK, and efficacy information, as well as the recommendations from the scientific committee.

The dose escalation of SGI-110 will follow a traditional 3+3 design Cohorts of 3-6 patients will receive a combination therapy of SGI-110 and Ipilimumab 3mg/kg. Each patient will receive SGI-110 s.c. for 5 consecutive days (D1-5) during a 3-week cycle at one of the following doses:

- Dose Level -1: 15 mg/m^2 day
- Dose Level 0: 30 mg/m^2 day
- Dose Level +1: 45 mg/m^2 day
- Dose Level +2: 60 mg/m^2 day

In the absence of dose-limiting toxicities (DLTs), the starting dose of SGI-110 of 30 mg/m^2 day will be escalated to 45 mg/m^2 day on Days 1-5. In the absence of DLT in Dose Level +1, the dose of SGI-110 of 45 mg/m^2 day will be escalated to 60 mg/m^2 day on Days 1-5 (Level +2). In the presence of 1 DLT in 3 subjects of the single dose cohort, the cohort will enroll 3 more subjects at the same dose level. In the event that 2 or more DLTs were encountered at the single dose cohort, the previous lower dose level will be evaluated. The MTD will be the highest SGI-110 Dose Level (15-60 mg/m^2 day on Days 1-5) in combination with ipilimumab at which no more than 1 of 6 subjects experiences a DLT. Once the MTD is established, additional subjects will be treated at that dose up to a total of 19 subjects in the entire study.

## **5.3 Dose-limiting Toxicity**

DLT is defined as any of the following events occurring during the first treatment cycle and clearly related to study treatment: grade 4 neutropenia (absolute granulocyte count < 0.5 x 10^9/L, ≥ 5 days), febrile neutropenia grade ≥ 3 (absolute granulocyte count < 1.0 x 10^9/L and fever ≥ 38.5° C), platelet count < 25.000/L or thrombocytopenic bleeding, AST or ALT grade ≥ 3 for 7 days, any grade 3 or 4 non-hematologic toxicity (excluding alopecia, non pre-medicated nausea and vomiting), grade 3 or 4 clinically

significant nausea, vomiting, or diarrhoea in the presence of maximal supportive care, a required interruption of treatment > 2 weeks due to toxicity. If the toxicity fails to resolve to  $\leq$  grade 2 with 14 days off treatment, the patient will be removed from the study.

Inability to initiate Cycle 2 within 2 weeks of scheduled treatment due to slow recovery from study drug-induced toxicities and failure to meet re-treatment criteria.

The DLT observation period is defined as the first 3 weeks of treatment, i.e., from Day 1 to Day 21 of Cycle 1. Once the MTD is reached in each group, the safety data will be analysed.

Note: All AEs (including those occurring after the end of the DLT observation period) will be considered for decision-making by the SMC.

**Tolerability** will be defined as the ability to continue treatment for at least 2 cycles in a row without development of DLTs.

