**Statistical Methods, Sample Size Considerations and Statistical Analyses:**

The phase 1 of SGI-110 in combination with ipilimumab is designed as a dose-escalation study. The primary end-point will be the, Maximum Tolerated Dose (MTD) and safety of the combination of SGI-110 plus ipilimumab.

Six patients will be treated at the first dose level for one cycle.

In the absence of dose-limiting toxicities (DLTs), the starting dose of SGI-110 of 30 mg/m^2 day (Dose Level 0) will be escalated to 45 mg/m^2 day (Dose Level +1) on Days 1-5. In the absence of DLT in Dose Level +1, the dose of SGI-110 of 45 mg/m^2 day (Dose Level +1) will be escalated to 60 mg/m^2 day (Dose Level +2) ) on Days 1-5 (Level +2). In the presence of 1 DLT in 3 subjects of the single dose cohort, the cohort will enroll 3 more subjects at the same dose level. In the event that 2 or more DLTs were encountered at the single dose cohort, the previous lower dose level will be evaluated. The MTD will be the highest SGI-110 Dose Level (15-60 mg/m^2 day on Days 1-5) in combination with ipilimumab at which no more than 1 of 6 patients experiences a DLT. Once the MTD is established, additional subjects will be treated at that dose up to a total of 19 subjects in the study. If no irDCR is observed the study may be terminated.

DLT is defined as any of the following events occurring during the first treatment cycle and clearly related to study treatment: grade 4 neutropenia (absolute granulocyte count  $< 0.5 \times 10^9 /L$ ,  $\geq 5$  days), febrile neutropenia grade  $\geq 3$  (absolute granulocyte count  $< 1.0 \times 10^9 /L$  and fever  $\geq 38.5^\circ C$ ), platelet count  $< 25.000/L$  or thrombocytopenic bleeding, AST or ALT grade  $\geq 3$  for 7 days, any grade 3 or 4 non-hematologic toxicity (excluding alopecia, non pre-medicated nausea and vomiting), grade 3 or 4 clinically significant nausea, vomiting, or diarrhoea in the presence of maximal supportive care, a required interruption of treatment  $> 2$  weeks due to toxicity. If the toxicity fails to resolve to  $\leq$  grade 2 with 14 days off treatment, the patient will be removed from the study.

No formal sample size calculation was done. Sample size will range from 6 to 19 patients.

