## **7.2 Dose-limiting Toxicities**

Dose-limiting toxicities are defined in Section 5.3.

All presumed DLTs (as defined in Section 5.3) must be recorded immediately, i.e., within a maximum of 24 hours after becoming aware of the event, in the eCRF irrespective of seriousness and the event must be specified as a DLT. In addition, serious DLTs must be reported in an expedited manner according to the procedure for SAEs, as outlined above. Unless an NCI-CTCAE Grade 4 hematologic or a Grade 3/4 non-hematologic toxicity that occurs during the DLT observation period is clearly due to a non-drug cause, the Investigator should consider all AEs seen during the DLT observation period (from Day 1 to Day 21 of Cycle 1) to be at least possibly related to the trial treatment. In addition, the methods described in Section 6.3.5 and 7.4 should be used to assess all AEs throughout the trial until after completion of the SFU Visit(s).

Section 4.1.3 outlines the responsibilities of the SMC with respect to DLTs.

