### **7.3 Assignment of Adverse Event Intensity and Relationship to Study Drug**

All adverse events, including those that are serious, will be graded according to the National Cancer CTCAE version 4.

The following categories and definitions of causal relationship to study drug as determined by a physician should be used for all NIBIT clinical study AEs:

- Related: There is a reasonable causal relationship to study drug administration and the AE
- Not related: There is not a reasonable causal relationship to study drug administration and the AE.

The expression "reasonable causal relationship" is meant to convey in general that there are facts (e.g., evidence such as de-challenge/re-challenge) or other arguments to suggest a positive causal relationship.

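### The DLT definition leaves attribution undetermined, contains two conditions that a broader clause overrides, and sets a platelet limit that cannot be met as written

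*Combined protocol and SAP*

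**What the plan says.** **Attribution.** Section 5.3 begins "DLT is defined as any of the following events occurring during the first treatment cycle and clearly related to study treatment". The synopsis (statistical methods) has the same condition: "occurring during the first treatment cycle and clearly related to study treatment". Section 7.2 refers to 5.3 for the definition, then sets a default for causality. Unless a grade 4 haematologic or grade 3/4 non-haematologic toxicity in the window "is clearly due to a non-drug cause, the Investigator should consider all AEs seen during the DLT observation period" "to be at least possibly related to the trial treatment". Section 7.3 gives two causality categories. One is "Related: There is a reasonable causal relationship to study drug administration and the AE"; the other is its negation.

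**Overlapping clauses.** The list in 5.3 requires grade 3 or higher AST/ALT to last 7 days, and grade 3-4 diarrhoea to occur despite maximal supportive care. It also counts "any grade 3 or 4 non-hematologic toxicity (excluding alopecia, non pre-medicated nausea and vomiting"), with no duration and no exception for AST/ALT or diarrhoea.

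**Platelets.** The criterion in 5.3, repeated in the synopsis, is "platelet count < 25.000/L or thrombocytopenic bleeding". Section 4.2.1 sets the eligibility floor at 100 x 10^3 per µL.

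**Use of the count.** Under 5.2.2, no DLT leads to escalation, 1 in 3 adds three patients, and 2 or more sends the study to the lower level. The MTD is the highest level with no more than 1 DLT in 6. Section 4.2.3 also lists a DLT as a reason for mandatory discontinuation.

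**The concern.** In cohorts of three to six, one reclassified event can change the decision. The definition should therefore let two readers with the same case records reach the same count. Here an event of uncertain cause, a short liver-enzyme rise, a diarrhoea episode without maximal supportive care, or a low platelet count may be classified differently, depending on which sentence the reader follows or how an unworkable limit is repaired.

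These are not remote events for the two drugs. Section 1.3.5.1 expects myelosuppression to determine the safe dose. Section 1.5 lists thrombocytopenia among the main SGI-110 reactions. Section 1.3.6.3 names colitis and diarrhoea as the most common grade 3-4 treatment-related events on ipilimumab. At stake is whether the MTD, part of the primary endpoint, can be reproduced from the recorded data.

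**Working it through.** The plan gives no DLT rate, error rate or sample-size calculation, so there is no figure of its own to reproduce.

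**1. Attribution.** Take a grade 3 non-haematologic event of uncertain cause on Day 15.

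| Section | Test | Result |
|---|---|---|
| 5.3, synopsis | clear relation to treatment? | no, so not a DLT |
| 7.2 | clearly a non-drug cause? | no, so at least possibly related |
| 7.3 | related or not related | one must be chosen; neither is tied to the wording of 5.3 or 7.2 |

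Nothing says whether an event recorded as related under 7.3 meets the 5.3 standard, so its DLT status is not determined.

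**2. Overlap.** The list is disjunctive: meeting one item is enough. A related grade 3 ALT rise of 2 days fails the AST/ALT item but meets the general item, so literally it counts. The 7-day condition then does no work, and the same holds for the supportive-care condition on diarrhoea. Suppose instead that those conditions were meant to limit. With three patients, no other DLT, and short grade 3 ALT rises judged related:

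| Patients with a short rise | Literal reading | 7-day condition limits |
|---|---|---|
| 1 | 1/3, add three | 0/3, escalate |
| 2 | 2/3, go down | 0/3, escalate |

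At six patients, the difference between 1/6 and 2/6 decides whether the level can be the MTD.

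**3. Platelets.** One litre is 10^6 µL.
- Read as 25,000 per litre: 25,000 / 10^6 = 0.025 per µL. Against the eligibility floor: 100,000 / 0.025 = 4,000,000.
- Read as a decimal, 25 per litre: 25 / 10^6 = 0.000025 per µL, and 100,000 / 0.000025 = 4,000,000,000.

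On either reading the count criterion cannot be met in practice, and only thrombocytopenic bleeding remains.

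**4. Sensitivity of the 3+3 rule (all rates assumed).** Let p be the DLT probability, and assume escalation after 0/3 or 1/6. The text states escalation only for no DLT.

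P(escalate) = (1-p)^3 + 3p(1-p)^2 x (1-p)^3
- p = 0.10: 0.729 + 0.243 x 0.729 = 0.906
- p = 0.20: 0.512 + 0.384 x 0.512 = 0.709
- p = 0.30: 0.343 + 0.441 x 0.343 = 0.494

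If only 0/3 escalates, the values are 0.729, 0.512 and 0.343.

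Now let p = 0.10 be the probability of an event that counts on every reading, and q that of an event that counts only on the wider one. For the first three patients:

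P(decisions differ) = [(1-p)^3 - (1-p-q)^3] + 3p[(1-p)^2 - (1-p-q)^2]

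P(escalate on one reading, go down on the other) = 3q^2(1-p-q) + q^3

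| q | decisions differ | escalate against go down |
|---|---|---|
| 0.05 | 0.141 | 0.007 |
| 0.10 | 0.268 | 0.025 |
| 0.15 | 0.381 | 0.054 |
| 0.20 | 0.482 | 0.092 |

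Results are nearly the same with p at 0.05 or 0.15.

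**The case against.** The strongest reply is that the DLT count does not act alone. Section 5.2.2 makes escalation depend also on non-DLT adverse events, PK, efficacy and the scientific committee's advice. Section 5.3 has the Safety Monitoring Committee consider all adverse events, including those after Day 21. Section 4.1.3 has that committee decide DLTs, escalation and the MTD by consensus. This stands as mitigation: ambiguous wording does not mechanically produce a different MTD. But no section tells the committee which wording governs, and the 1-of-6 criterion is stated in DLTs alone.

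Three stronger readings are tempting, and the documents do not support them.
- A reader might infer that 7.2 is a rival DLT definition. It is not: it defers to 5.3, and its presumption concerns causality. What remains is two attribution standards, neither mapped to the recorded categories.
- A reader might infer that a 2-day grade 3 ALT rise is both a DLT and not one. The list is disjunctive, so literally it counts. The defect is a condition without effect and an unclear intent.
- A reader might call per litre an impossible unit. It is valid, and the same sentence uses 10^9 per litre for granulocytes. The value is wrong on that scale, and staff may well see a slip and read through it.

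On size, the overlaps may involve few patients. Section 1.3.6.3 reports grade 3-4 colitis and diarrhoea in 3% to 5% on ipilimumab monotherapy at 3 mg/kg. Section 5.3.2 calls SGI-110 liver toxicity infrequent, possibly around Week 4 or 5, which is after the Day 1-21 window. These figures point to the lower end of the sensitivity range for the liver and gut clauses; they say nothing about the attribution conflict.

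**Conclusion.** The point holds as a defect of definition in three places: attribution is not determined for uncertain events, two conditions in 5.3 are inoperative as written, and the platelet count limit cannot be met. The platelet finding needs no assumption beyond reading the text as printed. The ALT example needs only the written 3+3 rule and events judged related; it shows that the same patients can lead to escalation or to the lower level.

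How often this would happen cannot be derived from the documents. The probabilities above rest on assumed rates, and the 0.91, 0.71 and 0.49 also on escalation after 1/6. They show how sensitive the rule is to the DLT rate, not how far the wording shifts that rate. A reader might infer that the choice of attribution wording would cut the DLT rate by some large factor, or that the trial would declare a different MTD. The documents support neither. They support that the MTD cannot be reproduced from the written definition, with committee consensus as a partial safeguard.

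**What to change.** The sponsor should make three changes, with the clinical team choosing every rule and value.
- Reconcile the synopsis, 5.3, 7.2 and 7.3 so that one attribution rule decides DLT status, and state which recorded category in 7.3 satisfies it.
- State in 5.3 and the synopsis whether the AST/ALT and diarrhoea clauses are exceptions to the general grade 3-4 non-haematologic clause, or delete the conditions that have no effect.
- Correct the platelet limit in both places so that value and unit agree with the scale used in 4.2.1.

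No rule or threshold is proposed here, because DLT status drives dose decisions and mandatory discontinuation. The cost is a wording amendment, and DLT counts may change slightly. It should be in place before any cohort is judged.
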